#### Explorative objective

Capillary leak assessment (plasma ADM)Plasma ADM amount and change to BLBlood plasma phenotyping: endothelial dysfunction and immunological characterizationAmount of von Willebrand factor (vWF), plasminogen activator inhibitor-1 (PAI-1), ICAM-1, VCAM-1, E-selectin, and change to BLIL-1α, IL-6, IL-10OMICs analysis focusing on immunological parametersQuality of life, healthcare use, and productivityEQ5D-5L score (also single questions) at day 28 and FUUse of healthcare resources and productivity assessed at FU

#### Safety

Safety parameters (evaluated for the safety set)Number of adverse events and serious adverse eventsType and severity (mild, moderate, severe) of (serious) adverse eventsSeriousness and relatedness of (S)AEsMean number per patient and total number of injection-related (S)AEs within 1 h after injection of IMPTreatment-related (S)AEs

Any clinical adverse event or abnormal laboratory test value that is serious, irrespective of the treatment received by the patient, must be reported to the sponsor by the investigator within 24 h of knowledge. We use the definition and reporting requirements according to local Drug Law, GCP, and ICH Guideline for Clinical Safety Data Management. As survival/death is one endpoint parameter, the integrity of the clinical trial may be compromised when the blind is systematically broken by reporting fatal and/or life-threatening SUSARs. Therefore, fatal and/or life-threatening SAEs that fulfil the following criteria will be treated as disease related and will not be subject to systematic unblinding and expedited reporting:Haemodynamic worseningLiver cytolysis/insufficiencyAcute renal failureDiffuse intra-vascular coagulation/bleedingsLeucopenia/thrombopenia/anaemiaSevere mesenteric ischaemiaBrain death/haemorragic stroke/ischaemic strokePulmonary embolismAcute myocardial infarction/cardiac rhythm disordersAspiration pneumonia/ventilator-acquired pneumonia/bacteraemia/fungaemia

Adverse events, especially those for which the relationship to test “drug” is “related”, should be followed up until resolved or until FU visit. If a clear explanation is established, it should be recorded on the CRF. Treatment of AEs is at the discretion of the investigator and should follow the standards of medical care at the investigator’s institution.

#### Insurance

Insurance cover is provided for damage to health that occurred no later than 10 years after completion of the clinical trial conducted on the insured person and is reported to the insurer no later than 10 years after completion of the clinical trial

#### Study management groups

IXION is embedded in the EU-founded project COVend. Therefore, infrastructure required for the EU project (e.g. Steering committee and data manager) according to the grand agreement will be used in IXION. To ensure the highest safety level, we established an external scientific advisory board, a risk assessment group, a data safety monitoring board, and an ethical advisory board.

#### Data safety monitoring board

A data safety monitoring board (DSMB) will be established for this study. The DSMB is an independent advisory group of experts with a mandate to periodically review blinded and unblinded safety data to allow ongoing judgment on the benefit and risk of the trial. The DSMB can recommend that the study should be stopped, temporarily suspended, or amended if it determines that the study is not meeting the necessary safety requirements (e.g. new information is available which changes the benefit-risk balance to the negative). The DSMB consists of physicians and scientists with clinical and scientific expertise in clinical studies.

To ensure a high level of data security, a GDPR data protection concept was established for the project. In addition, all participating partners must also have a data protection concept. Further information can be found in the respective data protection concepts.

#### Data access

During the course of the study, the medical study staff will of course have access to the eCRF (with pseudonymized data), as well as the data management, monitors, laboratory staff, PMO, sponsor, and project management (all blinded to the study medication). The Drug Safety Physician as well as the DSMB receive the required safety extracts from the database upon request or prior to a DSMB meeting and have the possibility to unblind the therapy data if necessary. Laboratory results for phenotyping of the blood plasma (ITMP laboratory) are transmitted monthly in CSV format and imported into the study database after conversion into XML format by the data management. The statistics receive the study data for evaluation, and after completion of the study, the sponsor receives the entire pseudonymized data and the investigators receive the data for their respective study centre (pdf files on data carriers). In any case, only pseudonymized data will be passed on.

During the study, only authorized representatives of the sponsor (e.g. CRAs and auditors) and the responsible monitoring authorities have access to personal health data (patient files at the study centre) in addition to the study personnel at the study centre.

After the completion of the study, no further studies are planned with the collected data and biological specimens.

### Sample size considerations

Based on our literature research [24–26], we estimate the frequency of patients who do not worsen their disease status under placebo (+SoC) to be 70%, since we include only hospitalized COVID-19 patients and not any ambulatory COVID-19 patients with mild disease state. We expect that FX06 (+SoC) improves this rate by approximately 15%. Following Spinner et al. and ICU estimations at the KGU Frankfurt, we also expect 15% less patients with progressed/worsened disease status in the group treated with FX06 (+SoC) compared to placebo (+SoC).

Applying a *Z*-test for proportions with continuity correction with a significance level of 5%, *n* = 291 patients (194 FX06: 97 placebo; without drop-outs) are required to demonstrate a treatment difference in the proportion of patients with progressed/worsened disease until day 28 with a power of 80%. Considering 5% drop-out, 306 (204 FX06: 102 placebo) patients need to be recruited.

Sample size was calculated with G*Power version 3.1.9.6 using the *Z*-test for the difference between two independent proportions with continuity correction. Sample sizes were reconfirmed using PASS 16.0.2.

### Statistical methods

The statistical analysis will be performed by the study statistician after termination of the study, when all included patients have finished their last visit, the data review process of the data management is completed, and the database is hard locked and when all data queries are resolved. Data will be unblinded after the database has been hard locked. The following presentation is a short summary of applied methods. A detailed description will be given in the provided additional files.

### Definition of population for analysis

The study includes eligible hospitalized non-intubated COVID-19 patients according to inclusion and exclusion criteria.

#### All randomized included patients (RS, randomized set)

The randomized set (RS) is defined to include all participating patients who were randomized into the study. Note that drop-outs of randomized patients will only occur if the patient does not take at least one dose of medication (these are not part of the analysis sets other than RS) and/or if the patient withdraws consent and/or if the investigator/PMO/sponsor withdraws the patient from the study. If a patient is withdrawn from the IMP, they are not withdrawn from study and therefore remain part of the analyses sets.

#### Full analysis set (FAS)

For the full analysis set (FAS) for the final analysis of the primary and secondary objectives, we will only consider the subgroup of all randomized included patients (RS) who had a baseline and one post-baseline assessment of their disease state based on the WHO score and who received at least one dose of FX06/placebo during the study. Otherwise, the considered primary endpoint and thus, the treatment effect, cannot be estimated under IMP use. Note that the FAS may be equal to the RS.

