#### Drop-outs

Drop-outs of randomized patients will only occur if the patient does not take at least one dose of medication (these are not part of the analysis sets other than RS) and/or if the patient withdraws consent and/or if the investigator/PMO/sponsor withdraws the patient from the study.

If a patient is withdrawn from the IMP, they are not withdrawn from study and therefore remain part of the analysis sets.

We expect a high intrinsic motivation from the patients. IXION is a medical class II study, conducted by professional study centres under monitor supervision. Furthermore, the study burdens for the patient are kept as low as possible, e.g. interim visits can be done remotely.

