#### Missing values

We do not expect many regular missing values due to the close visit windows and patient care. Collection of the WHO score up to day 28 will be tightly controlled for. In general, real missing data of a parameter will not be transformed and remains untouched unless stated otherwise. Summary statistics will be given including the underlying number of valid individual values and missing visit-wise.

We predefine the following measures for handling data of selected analyses:

All patients who die prior to day 28 will be given the corresponding highest WHO score (score of 10) for all remaining visits at and after assessment visit of their death for the purpose of assessing the primary endpoint and related sensitivity analyses even though no further patient data can be collected after visit of death. The date of death will be considered the time point for the time-to-event analyses. In case of drop-outs prior to day 28 or missing WHO scores of the FAS population prior to day 28 it will be evaluated, if a statistical deduction of the primary endpoint is possible independent of missing WHO scores, e.g. because the patient shows a worsened WHO score at some point, or no more than 3 consecutive visits show a worsened WHO score. If such a deduction of the primary endpoint is not possible, a decision on missing WHO scores may be deduced by taking a closer look at these cases at the blind data review meeting where all available information on the patient is evaluated in a blinded manner. All remaining patients of the FAS where no WHO score can be assigned will be considered missing for the primary analyses and will be considered by different scenarios as sensitivity analyses of the primary analysis (best/worse-case scenario and by LOCF). For all further endpoints, no imputation is planned currently.

Note that linear mixed models using maximum likelihood estimation are able to deal with missing values and are a valid alternative to imputation. As such, laboratory assessments are expected to be modelled accurately in terms of missing in LMMs.

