#### Statistical analyses

As primary analysis, we will compare the difference in proportion of patients with progressed/worsened disease state (as defined according to WHO score) until day 28 in both treatment groups (2-sample chi squared test). The aim is to demonstrate preliminary superiority of FX06 in prevention of worsened disease state in comparison to placebo (with standard of care) treatment. For the group comparison, the 5% significance level is considered.

With regard to secondary endpoints, these will be described by summary statistics stratified by treatment group and available visits and the treatment difference until day 28; the 95% confidence interval will be given. For selected secondary endpoints, linear mixed models will be applied to investigate the impact of treatment, time, treatment-by-time, and other factors such as demographics.

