## Discussion

### Bias and limitations

We expect a neglectable bias with regard to lack of compliance since all patients will be treated in hospital the entire time during the treatment period. Since we investigate the disease progression under FX06 treatment in several countries, a bias might arise when quality standard of care differs between countries. While this might impact the size of the primary endpoint, the assumptions on the treatment difference of the primary endpoint should not be impacted, since the randomization protects from imbalances within this regard within the different countries. Furthermore, as sensitivity analyses, endpoints will be compared descriptively among centres, or as effects of the regression models. Due to the double-blind study design, the risk of potential biases should be minimized.

Potential limitations might refer to a lack of recruiting and drop-out due to various possible protocol violations. While we controlled for drop-outs in the same size estimation, recruitment problems may be subject to external problems difficult to control for. One reason for the difficult recruitment are the competing ongoing trials on COVID-19, while at the same time a patient may not want to be assigned a placebo treatment although it represents standard of care.

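### Some dosed patients can be left out of the primary test, and those without a post-baseline WHO score fall outside every planned sensitivity scenario as well

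*Protocol article*

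**What the plan says.** The section on the full analysis set, which serves the primary and secondary objectives, admits only randomised patients "who had a baseline and one post-baseline assessment of their disease state based on the WHO score and who received at least one dose" of FX06 or placebo. The reason given is that the effect under study drug could not otherwise be estimated.

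The Missing values section then works in steps:
- Deaths before day 28 receive the highest WHO score, 10.
- For drop-outs and missing scores, the endpoint is deduced from the available scores where possible. Otherwise the case goes to a blinded data review.
- For what is left: "All remaining patients of the FAS where no WHO score can be assigned will be considered missing for the primary analyses". These patients enter best/worst-case and LOCF sensitivity analyses.

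The Drop-outs section counts as drop-outs patients who took no dose, patients who withdraw consent, and cases "if the investigator/PMO/sponsor withdraws the patient from the study". It states that patients withdrawn from study drug remain in the analysis sets. It does not say so for dosed patients withdrawn from the study. Bias and limitations expects "lack of recruiting and drop-out due to various possible protocol violations".

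**The concern.** Both conditions depend on what happens after randomisation. In patients who may be deteriorating, a missing score can be related to outcome and possibly to treatment. The stated reason for the FAS condition fits a patient who was never dosed. It does not fit a dosed patient whose score was not recorded.

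The planned checks leave two gaps. First, the scenarios are written for the remaining patients of the FAS, so a dosed patient excluded for lack of a post-baseline score is missing from the primary test and from every scenario. Second, the endpoint is a worsened score on three consecutive days. Under LOCF in its usual form, one last worsened score with at least two days left before day 28 becomes a three-day run and therefore an event. One last unworsened score with no earlier run becomes a non-event. The last observation tends to fix the answer, and nothing planned lies between that and the extreme bounds.

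At stake is whether a superiority result could depend on patients who were dosed but not counted.

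**Working it through.** **Inputs (Sample size considerations; Statistical analyses).** "we estimate the frequency of patients who do not worsen their disease status under placebo (+SoC) to be 70"%, so 30% worsen on placebo. FX06 is expected to have 15 percentage points fewer, so 15%. Allocation is 2:1. The calculation is "with continuity correction with a significance level of 5"% and "with a power of 80"%. The analysis section says "For the group comparison, the 5% significance level is considered". Neither place states sidedness; two-sided is inferred because it reproduces the stated size.

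**Reproducing the plan's figure.** With k=2 and pooled rate (0.30 + 2×0.15)/3 = 0.20:
- Uncorrected placebo n = [1.960·√(1.5×0.20×0.80) + 0.842·√(0.30×0.70 + 0.15×0.85/2)]² / 0.15² = 87.18.
- Corrected n = (87.18/4)·[1 + √(1 + 2×3/(87.18×2×0.15))]² = 96.9, so 97 placebo and 194 FX06, total 291, as stated. One-sided with correction gives 237.
- 291 × 1.05 = 305.55, so 306 (204:102), as stated. The allowance is 204−194 = 10 FX06 and 102−97 = 5 placebo patients.

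**Effect of the loss at the design effect.** Chi-squared without correction, equivalent to z = (p₁−p₂)/√[p̄(1−p̄)(1/n₁+1/n₂)]. With the 15 patients left out: 29/194 (14.9%) vs 29/97 (29.9%), p̄ = 58/291 = 0.199, z = −3.01, p = 0.0026. Adding them back:

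| Lost patients who worsened (FX06, placebo) | FX06 | Placebo | p |
|---|---|---|---|
| 0/10, 0/5 | 29/204 | 29/102 | 0.003 |
| 3/10, 2/5 (about the placebo rate) | 32/204 | 31/102 | 0.003 |
| 10/10, 5/5 | 39/204 | 34/102 | 0.006 |
| 8/10, 0/5 | 37/204 | 29/102 | 0.039 |
| 10/10, 1/5 | 39/204 | 30/102 | 0.042 |
| 9/10, 0/5 | 38/204 | 29/102 | 0.051 |
| 10/10, 0/5 (worst case) | 39/204 (19.1%) | 29/102 (28.4%) | 0.065 |
| 0/10, 5/5 (best case) | 29/204 | 34/102 | 0.0001 |

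With Yates correction the threshold is slightly lower: 8/10 with 0/5 gives p = 0.055, and 10/10 with 1/5 gives p = 0.059.

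**A weaker but significant result.** 35/194 (18.0%) vs 29/97 (29.9%) gives p = 0.021. If 5 of 10 lost FX06 and 1 of 5 lost placebo patients worsened, this becomes 40/204 (19.6%) vs 30/102 (29.4%), p = 0.054. At the edge, 38/194 vs 29/97 gives p = 0.049, and the full worst case 48/204 vs 29/102 gives p = 0.35.

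**Across trials.** In 100,000 simulated trials at the design rates, about 46% of significant results lost significance in the full worst case. About 6% did so when all lost patients in both arms counted as worsened.

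**The case against.** The strongest reply is that the text already closes most of the gap. Deaths are scored 10, patients taken off study drug stay in, drop-outs are resolved from available scores where possible, and the rest go to blinded review. Remote contact after discharge and tight control of WHO scores to day 28 should keep missing data low. All of this stands. A reader might call the primary analysis a completer analysis; the article does not support that.

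A reader might also take withdrawal by the investigator, project office or sponsor as a third exclusion rule. The article does not support this either. Exclusion from all sets other than the randomised set is attached only to patients who took no dose, and the Missing values section gives a procedure for drop-outs. A dosed, withdrawn patient is lost only without a post-baseline score or with an outcome that cannot be assigned. The remark on protocol violations is a comment on limitations. What remains is that the status of such patients is not spelled out.

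The worst case above is also of the kind the plan already lists, so the planned bounds would expose that fragility, but only for patients inside the FAS. Multiple imputation under missing-at-random would barely move p at the design effect (compare 3/10 and 2/5, p = 0.003) and does not address informative loss. That is why a tipping-point analysis is needed beside it. Finally, the article calls its methods a short summary, so LOCF details may sit elsewhere, but the FAS condition and the handling of unassignable outcomes are fixed in the article.

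**Conclusion.** The point holds in a limited form. Dosed patients can be left out of the primary test on post-randomisation grounds, and those without a post-baseline score are covered by no planned scenario. LOCF adds little for this endpoint.

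The exposure is small: if drop-out stays as planned, at most 5% (10 FX06 and 5 placebo, assuming the loss falls 2:1). That 5% also includes never-dosed patients and consent withdrawals, whom a wider FAS would not recover. So the table shows an upper limit, not what the change would restore. A reader might infer that the planned loss alone decides the conclusion. At the design effect it does so only in a near-extreme one-sided pattern; moderate or same-direction patterns leave p at or below 0.006. Fragility becomes a practical matter if the observed effect is smaller than planned. The figures assume a two-sided 5% test without continuity correction unless stated.

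**What to change.** 1. Define the FAS as all randomised patients who received at least one dose, analysed as randomised, without the post-baseline-score condition.
2. State that patients withdrawn from the study by the investigator, project office or sponsor stay in the FAS, and that WHO score (to day 28) and vital status (to day 60) continue to be collected unless consent is withdrawn.
3. Include every dosed patient with an undetermined outcome by multiple imputation using WHO stratum, centre or country, and the observed daily scores, either in the primary analysis or as a pre-specified sensitivity analysis.
4. Keep the best/worst-case bounds, extend them to all dosed patients, and replace LOCF with a tipping-point analysis over the number of worsened patients among the undetermined in each arm.

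The cost is protocol and analysis-plan wording, a little more programming, and imputation assumptions for about 5% of patients or fewer. The sample size need not change.

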#### Per-protocol population

Per protocol population (PP) is defined as the subset of the FAS excluding those patients with major protocol violations occurring up to day 28. Specific reasons for warranting exclusion will be documented prior to the closing of the database. Not all protocol deviators and violators will be excluded from the per protocol population.

#### Safety-population

The safety analysis set is defined as all randomized patients who received at least one dose of FX06/placebo during the study. This population is a subset of all randomized included patients (RS) and will be used for all safety analyses.

#### Drop-outs

Drop-outs of randomized patients will only occur if the patient does not take at least one dose of medication (these are not part of the analysis sets other than RS) and/or if the patient withdraws consent and/or if the investigator/PMO/sponsor withdraws the patient from the study.

If a patient is withdrawn from the IMP, they are not withdrawn from study and therefore remain part of the analysis sets.

We expect a high intrinsic motivation from the patients. IXION is a medical class II study, conducted by professional study centres under monitor supervision. Furthermore, the study burdens for the patient are kept as low as possible, e.g. interim visits can be done remotely.

#### Missing values

We do not expect many regular missing values due to the close visit windows and patient care. Collection of the WHO score up to day 28 will be tightly controlled for. In general, real missing data of a parameter will not be transformed and remains untouched unless stated otherwise. Summary statistics will be given including the underlying number of valid individual values and missing visit-wise.

We predefine the following measures for handling data of selected analyses:

All patients who die prior to day 28 will be given the corresponding highest WHO score (score of 10) for all remaining visits at and after assessment visit of their death for the purpose of assessing the primary endpoint and related sensitivity analyses even though no further patient data can be collected after visit of death. The date of death will be considered the time point for the time-to-event analyses. In case of drop-outs prior to day 28 or missing WHO scores of the FAS population prior to day 28 it will be evaluated, if a statistical deduction of the primary endpoint is possible independent of missing WHO scores, e.g. because the patient shows a worsened WHO score at some point, or no more than 3 consecutive visits show a worsened WHO score. If such a deduction of the primary endpoint is not possible, a decision on missing WHO scores may be deduced by taking a closer look at these cases at the blind data review meeting where all available information on the patient is evaluated in a blinded manner. All remaining patients of the FAS where no WHO score can be assigned will be considered missing for the primary analyses and will be considered by different scenarios as sensitivity analyses of the primary analysis (best/worse-case scenario and by LOCF). For all further endpoints, no imputation is planned currently.

Note that linear mixed models using maximum likelihood estimation are able to deal with missing values and are a valid alternative to imputation. As such, laboratory assessments are expected to be modelled accurately in terms of missing in LMMs.

Unless stated otherwise, values below/above the LOQ will in general be imputed by a suitable fixed value (e.g. LLOQ, ULOQ, Zero), depending on the nature of the laboratory value and its time of assessment. If a large number of measurements of a laboratory parameter falls above/below the LOQ, alternative methods will be considered. SARS-CoV-2 antibodies below the threshold (LOQ) will be defined as 0/not present for the purpose of analyses.

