### Study objectives

#### Primary objective and endpoint

The primary objective is to demonstrate a difference in the proportion of patients with progressed/worsened disease state in patients receiving FX06 compared to patients receiving placebo until day 28.Proportion of patients with worsened disease state until day 28 in both treatment groups

Progression/worsening of disease state will be defined as a worsened WHO score on 3 consecutive days (always compared to the BL WHO score) until day 28 (e.g. a WHO score of 5 on 3 consecutive days for a patient that had a WHO score of 4 at BL will be defined as a worsened disease)

The assessment of disease severity and progression by the WHO score was chosen based on the recommendation of the WHO [23] to include this score for all COVID-19 clinical trials. Furthermore, for this international, multicentre study, it facilitates comparable and objective assessment of disease severity across study centres.

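### The two example cases for settling the primary outcome despite missing WHO scores contradict the three-day endpoint definition and, for short runs, each other

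*Protocol article*

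**What the plan says.** **Definition.** Protocol article, Primary objective and endpoint: "Progression/worsening of disease state will be defined as a worsened WHO score on 3 consecutive days", always against the baseline score and up to day 28. The example there reads "a WHO score of 5 on 3 consecutive days for a patient that had a WHO score of 4 at BL will be defined as" worsened, so a run of exactly 3 days is an event.

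**Missing scores.** Protocol article, Missing values. The procedure is announced as predefined and covers these patients: "In case of drop-outs prior to day 28 or missing WHO scores of the FAS population prior to day 28". It has three steps.

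1. Evaluate whether the primary outcome can be deduced without depending on the missing scores. Two cases are given as examples: "because the patient shows a worsened WHO score at some point, or no more than 3 consecutive visits show a worsened WHO score".
2. If not, "a decision on missing WHO scores may be deduced by taking a closer look at these cases at the blind data review meeting".
3. Patients still without an assignable score are missing in the primary analysis and enter best/worst-case and LOCF sensitivity analyses.

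The same section gives patients who die before day 28 a WHO score of 10 for all visits from death onward.

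**The concern.** The examples in step 1 are the only concrete content the article gives for the deduction, and neither uses the threshold of the endpoint. The first requires no duration. The second allows a run that the definition already counts as an event, and it counts visits where the definition counts days.

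The order of the steps makes this matter. Blind review and the sensitivity analyses take only patients whose outcome could not be deduced. A patient settled wrongly at step 1 goes straight into the primary chi-squared comparison, and no later step is designed to find the error. Patients with complete and with incomplete scores could then be judged by different endpoints.

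**Working it through.** **1. Side-by-side comparison.** Let L be the longest observed run of days worse than baseline. The article does not print the outcome belonging to each example. The natural reading is worsened for the first case and not worsened for the second.

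| L | Endpoint definition | First case (any worsened score) | Second case (at most 3) |
|---|---|---|---|
| 0 | no event observed | silent | not worsened |
| 1 or 2 | 3-day criterion not met | worsened | not worsened |
| 3 | event | worsened | not worsened |
| 4 or more | event | worsened | silent |

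At L = 1 or 2 the first case goes beyond the definition. At L = 3 the second case contradicts it. From L = 1 to L = 3 both cases apply and disagree. The examples fit the definition without conflict only at L = 0 and L ≥ 4, and at L = 0 only if no gap is long enough to hide 3 worsened days.

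**2. The plan's own figure.** The examples carry no number, so the reference point is Sample size considerations: 30% worsened on placebo (100% − 70%), 15% on FX06, 97 and 194 patients, 5% level, continuity correction. Sidedness is not stated; two-sided reproduces the result.

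- Corrected difference: 0.15 − 0.5 × (1/97 + 1/194) = 0.1423
- Pooled rate: (97 × 0.30 + 194 × 0.15)/291 = 0.20
- Null SE: √[0.20 × 0.80 × (1/97 + 1/194)] = 0.0497
- Alternative SE: √[0.30 × 0.70/97 + 0.15 × 0.85/194] = 0.0531
- Power: Φ[(0.1423 − 1.96 × 0.0497)/0.0531] = 0.800

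The stated 291 is reproduced, and the concern does not change it.

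**3. Illustration of direction.** The following shares are assumptions; none is in the document. Let m be the share of patients with gaps, f the share of their true non-events with 1 or 2 worsened days, and e the share of their true events with a run of exactly 3. All are taken as equal in both arms. Under one consistent order only one error can occur. If the first case decides, a run of 3 is correctly an event. If the second decides, runs of 1 or 2 are correctly non-events.

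- First case decides: observed rate = p + m(1 − p)f, and the difference shrinks to 0.15 × (1 − mf).
- Second case decides: observed rate = p(1 − me), and the difference shrinks to 0.15 × (1 − me).

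| Deciding case | m | f or e | Placebo | FX06 | Power |
|---|---|---|---|---|---|
| First | 5% | f = 10% | 30.35% | 15.43% | 0.79 |
| First | 10% | f = 20% | 31.4% | 16.7% | 0.76 |
| First | 20% | f = 30% | 34.2% | 20.1% | 0.69 |
| Second | 5% | e = 10% | 29.85% | 14.93% | 0.80 |
| Second | 10% | e = 20% | 29.4% | 14.7% | 0.79 |
| Second | 20% | e = 20% | 28.8% | 14.4% | 0.78 |

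The difference shrinks in every row. The table shows direction and sensitivity; it does not estimate what will happen in this trial.

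**The case against.** The strongest reply is that the two cases are examples. The governing test is that the outcome must follow whatever the missing scores are, and applied faithfully that test gives the right answer. The authors may well have meant worsening as defined, and fewer than 3. The article also expects few missing values, promises tight control of WHO score collection, plans for 5% drop-out and allows remote contact after discharge. Much of this stands: the principle is sound, and the number of affected patients may be small. It does not rescue the examples, which point away from the principle they illustrate. Nor is this detail left to a fuller document, since the article states the cases and they conflict with its endpoint.

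Three stronger readings are tempting but unsupported.

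- **A missing day always breaks a run.** A reader might infer that worse–missing–worse is classed as not worsened because the second case counts visits. Nothing says so. That outcome depends on the missing day, so under the general principle it is not deducible and goes to blind review.
- **A definite share of patients will be misclassified, in both directions.** The document gives neither a gap rate nor a distribution of run lengths. Adding the two errors together would also require the cases to be applied in inconsistent order.
- **The errors favour one arm because gaps follow deterioration or discharge.** This is undocumented. Deaths have their own scoring rule, post-discharge information can be obtained remotely, and the data review is blinded.

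**Conclusion.** The concern holds as a contradiction in the text. Taken literally, both example cases depart from the endpoint definition, and they conflict with each other for runs of 1 to 3. This needs no calculation and no assumption beyond the natural reading of which outcome each case implies.

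Misclassification is possible, not certain, because a careful analyst could follow the principle and ignore the examples. It can affect only patients with gaps or early exit, and its size cannot be determined from the document. If errors are equally common in both arms, the effect is dilution and some loss of power rather than a spurious benefit. The sample size of 291 evaluable and 306 recruited is not affected. The passage should be corrected because it governs the primary outcome and the later safeguards do not cover patients already settled.

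**What to change.** Before unblinding, replace the two examples with a rule that follows from the definition:

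- **Worsened:** at least 3 consecutive days observed worse than baseline, with the existing score of 10 applied after death.
- **Not worsened:** no run of 3 worsened days would arise even if every missing day up to day 28 were set to worsened.
- **Undetermined:** everyone else, who goes to the blind review and then to the missing-data steps already planned.

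Count days, not visits, throughout. Under this rule a gap of 3 or more days always leaves a patient undetermined unless an event has already been observed. A patient last observed on day 25 or earlier is therefore undetermined without one (28 − 25 = 3 days unseen).

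No separate clause making every death by day 28 an event should be added. A death on day 27 contributes at most two scored days (27 and 28), so under the present text it need not complete a run of 3. Such a clause would change the endpoint.

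The cost is a sentence or two in the protocol and the analysis plan. No new data are needed and the sample size does not change.
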